### Blinding

All patients will be blinded to the treatment to which they are allocated, thus peripheral blood is drawn even if they are assigned to the control group. All outcome assessors (orthopedists and radiologists) will be blinded, but the radiologists applying the treatment will not.

### Adverse events

The patients will be instructed to record any discomfort and/or any adverse reaction or event, whether or not it is related to the intervention. The investigator will evaluate and record the seriousness, intensity, expectedness, and causality relationship, and a written communication will be sent to the sponsor. Pertinent adverse events will be notified to the licensing authorities (Ethics Committee of HUC and Spanish Agency of Medicines) by fax or email.

### Statistical analysis

Categorical variables will be presented as rates and percentages. Demographic and clinical baseline characteristics will be assessed to confirm comparability between groups. If any clinically relevant data are unbalanced, we will perform an adjusted analysis. Categorical variables will be presented as frequencies and percentages, and we will use the mean and standard deviation for data with a normal distribution and median and interquartile range for non-parametric data. Potential efficacy analysis will be performed as intention to treat, comparing the percentage of patients that have achieved therapeutic success in each group using the chi-squared test with *P* < 0.05 deemed statistically significant. All statistical analysis will be performed using the SAS 9.2 version.

## Discussion

The present study had three principal objectives: first, to investigate if pure PRP interventions reduce symptoms and improve function by using the patient self-reported DASH-E questionnaire; second, to examine the clinical efficacy of needling combined with PRP injections in pain; and third, to identify the potential structural changes in the tendon after PRP treatment.

Multiple commercial protocols to prepare PRP are currently available on the market. Depending on the specific preparation protocol the qualitative and quantitative composition of PRP varies, and most likely so do the biological effects. Current experimental research postulates different efficiency among PRP formulations [15,16], mainly leukocyte-rich PRP (L-PRP) and leukocyte-depleted PRP (pure PRP). In fact, experimental research has shown that L-PRP is more pro-inflammatory when injected in rabbits [15], and it increases the levels of metalloproteases when assayed in tenocyte cultures compared to pure PRP [17].

On the basis of these preliminary experimental results, and the clinical results in the conservative management of knee OA in which L-PRP injections induced more transient post-injection swelling and pain than pure PRP [18], we expect fewer adverse reactions using pure PRP (leukocyte-depleted).

To date, all controlled clinical trials in epicondylitis have been performed with L-PRP [4-9]. In this pilot study, we aim to examine the efficacy of pure PRP, and potential comparative efficacy studies (L-PRP *vs.* pure PRP) would be performed in a subsequent step forward. Moreover, when compared to published clinical protocols performed with L-PRP, we might anticipate improved function and reduced pain using pure PRP associated with the needling intervention.

Additionally, there is no consensus about the frequency and number of PRP treatments in chronic injuries. Thus, whether two interventions would be more efficient than a single PRP application remains to be clarified. Previous studies in tendinopathy have not found any structural change after one PRP injection pointing out that one single intervention may be insufficient to induce structural changes [19,20]. In this pilot study we will explore whether two injections could modify the structural characteristics of the injured tendon. In addition, the optimal volume of PRP has not been defined so far thus we will adjust the injected volume (3–5 mL) to the individual anatomical characteristics.

The results of this study will provide insights into the effect of pure PRP in tendons and may contribute to identifying the best protocol for PRP application in tendinopathies.

## Trial status

Recruitment commencement is planned by January 2014 and the expected average enrollment rate is four patients every month. Data collection will continue for one year after the last recruited patient.

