## Methods/Design

### Study design

B-PRPtendon is a patient and assessor blinded superiority-type randomized controlled trial; the study will be conducted at Hospital Universitario Cruces (HUC). The research protocol is approved by the Ethics Committee of HUC and authorized by the Spanish Agency of Medicines. A total of 80 patients will be randomly allocated into one of two groups. The two groups are: US-guided percutaneous needling tenotomy combined with PRP injection each alternate week for a total of two interventions; and US-guided needling tenotomy combined with lidocaine injection each alternate week for a total of two interventions.

The study will run for 2 years. Recruitment will be for 12 months with final follow-up at 1 year post treatment (Table 1).

**Table 1 T1:** Outcome assessments

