### Sample size

The minimum sample size required to achieve scientifically valid results is 80. This sample size provides an 80% potency to detect any significant difference between the success rates in both groups (*P*1 = 0.93 and *P*2 = 0.65) with a level of significance of 5%, being each arm formed by 40 patient. We have assumed that the relative improvement with the PRP intervention is 1.43, assuming that the differences between PRP and lidocaine would be similar to the differences reported with corticoids [8], and a patient loss of approximately 20%. However, this is a randomized study which will help to gain insights into feasibility of recruitment, and into the number of patients who become lost to follow-up.

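### At four patients a month, 12 months of recruitment yields 48 patients, not 80; the accrual rate, recruitment window and sample size must be reconciled

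*Protocol article*

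**What the plan says.** Three sections of the protocol article bear on accrual.

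- **Study design** plans for 80 patients in total and fixes the calendar: "The study will run for 2 years. Recruitment will be for 12 months with final follow-up at 1 year post treatment".
- **Sample size** makes 80 a floor: "The minimum sample size required to achieve scientifically valid results is 80". The split is 40 per arm. The planning success rates are 0.93 and 0.65, with a 5% significance level, 80% power and a patient loss of about 20%.
- **Trial status** plans to start recruiting by January 2014 and says that "the expected average enrollment rate is four patients every month". It runs data collection until a year after the final patient is recruited.

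No section connects the monthly rate to the 12-month window. None says what happens if the window ends before 80 patients are in.

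**The concern.** The rate, the window and the target are linked by one multiplication, so fixing any two determines the third. As written, the three disagree by 32 patients, which is 40% of the target. At least one of them is therefore wrong.

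What is at stake depends on which figure gives way. If the calendar is binding, the trial stops at 60% of the size that it calls the minimum, and the stated power is not delivered. If the target is binding, the power is safe but the trial lasts about a third longer than stated. If the rate is the error, nothing else changes, but the plan needs a higher rate than any it states. Because no governing figure is named, the choice would be made once recruitment is already behind.

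**Working it through.** **Inputs**

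| Input | Value | Section |
|---|---|---|
| Target | 80, 40 per arm | Sample size |
| Recruitment window | 12 months | Study design |
| Study duration | 2 years (24 months) | Study design |
| Follow-up | 1 year | Study design; Trial status |
| Accrual rate | 4 a month | Trial status |
| Success rates | 0.93 v 0.65 | Sample size |
| Significance level | 5%; sidedness not stated, two-sided assumed | Sample size |
| Loss | about 20% | Sample size |
| Primary test | chi-squared | Statistical analysis |

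**Step 1: accrual**

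- Patients in the window: 4 × 12 = 48, or 24 per arm. Shortfall: 80 − 48 = 32. Share of target: 48/80 = 60%.
- Months needed for 80: 80/4 = 20. With one year of follow-up: 20 + 12 = 32 months, against 24 stated.
- Rate needed for 80 in 12 months: 80/12 = 6.7 a month, which is 6.67/4 = 1.67 times the stated rate.

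**Step 2: reproduce the stated 80% power**

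The normal approximation with pooled variance under the null and no continuity correction is

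power = Φ[(d − z·SE0)/SE1], with SE0 = √(2·p̄(1 − p̄)/n) and SE1 = √((p1(1 − p1) + p2(1 − p2))/n).

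Here d = 0.93 − 0.65 = 0.28, p̄ = 0.79 and z = 1.96, so 2·p̄(1 − p̄) = 0.3318 and the sum in SE1 is 0.0651 + 0.2275 = 0.2926.

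Forty per arm less 20% leaves 32 evaluable. Then SE0 = 0.1018 and SE1 = 0.0956, and the power is Φ(0.841) = 80.0%. This matches the protocol. The exact power of the uncorrected chi-squared test, by binomial enumeration, is 82.8%.

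**Step 3: power if enrolment stopped at 48**

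After 20% loss, 24 × 0.8 = 19.2, taken as 19 evaluable per arm.

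| Evaluable per arm | Situation | SE0 | SE1 | Formula | Exact |
|---|---|---|---|---|---|
| 32 | 80 enrolled, 20% loss | 0.1018 | 0.0956 | Φ(0.841) = 80.0% | 82.8% |
| 24 | 48 enrolled, no loss | 0.1176 | 0.1104 | Φ(0.449) = 67.3% | 71.7% |
| 19 | 48 enrolled, 20% loss | 0.1321 | 0.1241 | Φ(0.169) = 56.7% | 59.4% |

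Using 19.2 instead of 19 gives 57.2% by formula.

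**Step 4: sensitivity to the sidedness assumption**

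A one-sided test without continuity correction gives 88.0% at 32 per arm, so it does not reproduce the stated figure. A one-sided test with continuity correction (subtract 1/n from d, z = 1.645) does: 80.2% at 32 per arm. On that basis, 24 per arm gives 65.8% and 19 per arm 53.2%. Either route to the stated 80% therefore shows a similar drop.

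**Step 5: power if recruitment runs to 80**

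The number per arm is as planned, so the power stays at 80%. What changes is recruitment (20 months instead of 12) and total duration (about 32 months instead of 24).

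**The case against.** A reader might infer that this trial will have power of about 60%. The documents do not support that. The figure requires recruitment to close at 12 months with 48 enrolled, and nothing says that it would close short of 80. Study design gives the 12-month window but also the total of 80. Sample size treats 80 as a minimum. Trial status ties the end of data collection to the final patient, not to a date. On that reading the consequence is an overrun, and power is unaffected. A bare figure of about 60% also hides that the 20% loss has been applied, and it sets an exact result beside a protocol figure that an approximation reproduces. The like-for-like exact baseline is 82.8%.

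The rate is also a forecast of an average. Sample size says the study will inform the feasibility of recruitment, and the Discussion calls it a pilot, so the pace was not treated as settled. The endpoint, test, randomisation and patient safety are untouched.

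These points stand as limits on the consequence and the severity. They do not remove the contradiction. An expected average is exactly what determines a 12-month total, and a gap of 40% of the target is not rounding. Nor is this detail that an article would leave to a fuller document, because all of the conflicting figures are stated in the article itself.

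**Conclusion.** The contradiction is established by arithmetic on stated figures and needs no assumption. Four a month gives 48 patients in 12 months, and 80 requires either about 20 months of recruitment or about 6.7 a month. The documents do not show which figure is wrong.

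The effect on power is conditional. It arises only if recruitment closes on the calendar with 48 enrolled, and its size rests on the protocol's success rates, the assumed two-sided 5% test and the chosen loss: about 57% by formula (59% exact) after 20% loss, or 67% (72% exact) with none. The alternative is an overrun of about eight months with power intact.

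Severity: should fix. A stated design figure is wrong whichever reading is taken, but a timeline contradiction does not by itself undermine the trial's conclusion.

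**What to change.** 1. State in Study design that recruitment closes when 80 patients have been randomised, not on a calendar date.
2. Make the remaining figures agree with that, in one of two ways:
   - keep four a month, and restate recruitment as about 20 months and total duration as about 32 months; or
   - keep 12 months and two years, correct the rate to about 6.7 a month, and justify that it can be achieved.

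Reducing the sample size to fit the calendar is not a sound remedy. It would write 48 patients into a plan whose Sample size section sets 80 as the minimum.

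Cost: a wording change in Study design and Trial status, with no new procedures and no patients beyond 80. If four a month is right, the study also runs about eight months longer (32 − 24), a third more than the planned duration. If the rate is corrected instead, the cost is whatever recruitment effort the higher rate needs.
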